### Outcome measures

The primary end point of this study is the patency rate (stenosis of at least 50 % of the luminal diameter) on catheter or CT angiography or <2.5 of peak systolic velocity ratio (PSVR; peak systolic velocity within the area of stenosis divided by peak systolic velocity in a normal adjacent proximal artery segment) in the treated segment at 12 months after the intervention.

The secondary end points are as follows: (1) geographic miss rate (mild, moderate, severe); geographic miss refers to stent deployment to any area of the vessel that was intended to be treated with the stent but was not covered, or protrusion due to stent jumping, and/or elongation. Geographic miss rate is classified as 5–15 mm (mild), 15–25 mm (moderate), >25 mm (severe), or additional stent deployment over the stent deployment area that was not covered, or protrusion from the intended stent deployment area; (2) incidence of stent fracture; (3) limb salvage rate free of above-the-ankle amputation; (4) sustained clinical improvement rate at 12-month follow-up; (5) repeated target lesion revascularization (TLR) rate; (6) repeated target extremity revascularization (TER) rate; (7) total reocclusion rate; (8) comparison of angiographic variables including late loss and binary restenosis rate; (9) ABI at 12 months; (10) the rate of major adverse cardiovascular event (MACE), defined as composite of all-cause death, myocardial infarction, repeat percutaneous coronary intervention (PCI), and stroke at 12 months.

The detailed definitions are summarized in the Appendix.

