#### Sample size calculation

Although patency definitions varied across trials, 1-year patency rates in aortoiliac lesions were approximately 90 % on average from previous studies including CRISP-US and MELODIE [22, 23]. In the case of the SCUBA™ stent, the 9-month patency rate for the SCUBA™ stent was 99.2 % in the ACTIVE study - a prospective, multicenter, single-arm study that defines the midterm efficacy of a next-generation cobalt-chromium iliac stent for the treatment of de novo and restenotic lesions in iliac arteries [25]. However, a different definition - a ratio of <2.4 between the duplex peak systolic velocity in the treated vessel segment and the reference systolic velocity - was used, unlike the more common definition. There are limited data on the 1-year primary patency rate of the SCUBA™ stent. Based on the MELODIE trial [23], and the European multicenter iliac stent trial [26], the 1-year primary patency of the SCUBA™ stent was estimated to be 88 %, and the COMPLETE-SE™ stent was estimated to be 94.7 % in the CRISP-US trial. Therefore, the self-expandable COMPLETE-SE™ stent group will be the control group, and the balloon-expandable SCUBA™ stent group will be the experimental group.

Patency rate will be defined as absence of occlusion and absence of >50 % stenosis in the treated segment by quantitative coronary angiography (QCA) or if invasive angiography is not performed, PSVR ≤2.5 when evaluated with duplex ultrasound. On the basis of previous studies [22, 23], we hypothesize that the expected patency rate after stent deployment at 1 year would be 90 % for the self-expandable stent group, and 88 % for the balloon-expandable stent group, respectively. The predetermined noninferiority margin δ is a 10 % difference between treatment groups. There was clinical consensus that this noninferiority margin would be acceptable if safety is maintained and patients are treated more easily, regardless of stent classification. The power analysis is based on a noninferiority principle. The statistical significance level is 2.5 % at one side, the power of the test is set as 80 %, and the randomization ratio is set as 1:1. The test for proportion and the chi-square method will be used. Using standard sample size formula, it was calculated that 120 patients per group are needed for a total of 288 patients, after accounting for a 20 % dropout rate.

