## Appendix

### 1. End points definitions

- Primary patency: defined as stenosis of at least 50 % of the luminal diameter according to the worst angiographic view at the narrowest site within the treated segment plus the 10-mm segments proximal and distal to the treated segment by catheter angiography or CT angiography; PSVR ≥2.5 (PSVR = peak systolic velocity within the area of stenosis divided by peak systolic velocity in a normal adjacent proximal artery segment) or total occlusion by duplex ultrasound
- Geographic miss according miss grade (mild, moderate, severe): geographic miss is classified as 5–15 mm (mild), 15–25 mm (moderate), >25 mm (severe), or additional stent deployment over the stent deployment area that was not covered, or protrusion from the intended stent deployment area
- Stent fracture rate according fracture grade (minor, moderate, severe), [28] plain X-ray examinations for the stent fracture are used or performed using at least two different angulations (30 to 45° difference) and the highest available magnification. Stent fracture is classified as minor (single strut fracture), moderate (fracture of more than two struts), or severe (complete separation of stent segments)
- Target lesion revascularization (TLR): defined as any repeat percutaneous intervention of the target lesion or bypass surgery of the target vessel performed for restenosis because of a return of ischemic symptoms, decrease of at least one Rutherford category, decrease in the ankle brachial index of >0.15, or restenosis of >50 % as measured by catheter angiography. The target lesion is defined as the treated segment from 10 mm proximal to the stent and to 10 mm distal to the stent
- Target extremity revascularization (TER): defined as any repeat percutaneous intervention of the target extremity or bypass surgery of the target extremity performed for restenosis because of a return of ischemic symptoms, decrease of at least one Rutherford category, decrease in the ankle brachial index of >0.15, or restenosis of >50 % as measured by catheter angiography
- Limb salvage: defined as survival free of amputation. Amputation is defined as above-ankle amputation of the index limb

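### The primary end point is stated partly in reverse, and once the direction is corrected its definitions still differ on cut-offs, segment and CT angiography

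*Protocol article*

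**What the plan says.** The protocol article defines patency in four places.

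- **Outcome measures:** "The primary end point of this study is the patency rate (stenosis of at least 50" % of the lumen, "on catheter or CT angiography or <2.5 of peak systolic velocity ratio", in the treated segment at 12 months. The section sends the reader to the Appendix for detailed definitions.
- **Appendix 1 (End points definitions):** "Primary patency: defined as stenosis of at least 50" %, assessed "within the treated segment plus the 10-mm segments proximal and distal to the treated segment by catheter angiography or CT angiography". The duplex alternative is PSVR of 2.5 or more, "or total occlusion by duplex ultrasound".
- **Sample size calculation:** "Patency rate will be defined as absence of occlusion and absence of >50" % stenosis in the treated segment by quantitative angiography (QCA), or, "if invasive angiography is not performed, PSVR ≤2.5 when evaluated with duplex ultrasound".
- **Appendix 3 (QCA data definition and variables):** patency is listed as less than 50%.

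Three other sections bear on how these are used. Randomization and interventions recommends catheter angiography, CT angiography or duplex at 12 months according to local practice. Statistical analysis bases noninferiority on the difference in the proportions of patent patients, with a lower 95% confidence limit above -10 points. It also excludes missing data on the major end points.

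**The concern.** This is the only end point behind the noninferiority decision, so its definition has to give one answer per patient. As written it does not. Outcome measures scores angiography and duplex in opposite directions within one sentence, and Appendix 1 describes loss of patency throughout while calling it patency.

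Restoring the direction is not enough. The sections also differ on the two cut-offs, on whether the segment includes the edges, and on CT angiography. Sites may choose the imaging method and missing primary outcomes are left out, so these differences can affect both how a patient is classified and whether the patient is counted.

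**Working it through.** **Step 1. The rules side by side, as written.**

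| Section | Angiography: called patent if | Duplex: called patent if | Segment | CT angiography |
|---|---|---|---|---|
| Outcome measures | stenosis ≥50% | PSVR <2.5 | treated segment | named |
| Appendix 1 | stenosis ≥50% | PSVR ≥2.5 or total occlusion | plus 10 mm at each end | named |
| Sample size calculation | no occlusion, no stenosis >50% | PSVR ≤2.5, if no invasive angiography | treated segment | not named |
| Appendix 3 | <50% | not covered | not stated | not covered |

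**Step 2. Example patients, read literally.**

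| Patient | Outcome measures | Appendix 1 | Sample size calculation | Appendix 3 |
|---|---|---|---|---|
| Catheter, 60% stenosis | patent | patent | not patent | not patent |
| Catheter, 30% stenosis | not patent | not patent | patent | patent |
| Duplex, PSVR 2.0 | patent | not patent | patent | – |
| Duplex occlusion, no measurable PSVR | no rule | patent | not patent | – |

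**Step 3. What literal Outcome measures scoring does to the planned difference.** The inputs are the planning rates in the Sample size calculation: 90% patent for self-expandable and 88% for balloon-expandable, so 10% and 12% not patent. Let w be the share of patients assessed by angiography and assume it is equal in both arms. The article gives no value for w. For this illustration the planning rates are taken to apply under either imaging method.

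- Self-expandable: 10w + 90(1 - w) = 90 - 80w
- Balloon-expandable: 12w + 88(1 - w) = 88 - 76w
- Difference (balloon-expandable minus self-expandable): -2 + 4w points

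| w | Self-expandable | Balloon-expandable | Difference |
|---|---|---|---|
| 0 | 90% | 88% | -2 |
| 0.5 | 50% | 50% | 0 |
| 1 | 10% | 12% | +2 |

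Literal Appendix 1 scoring, reversed for both methods, gives 12 - 10 = +2 whatever the mix.

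**Step 4. What remains after the direction is corrected.** Read the criteria of stenosis of at least 50% (Outcome measures, Appendix 1) and PSVR of at least 2.5 or occlusion (Appendix 1) as failures.

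| Patient | Outcome measures | Appendix 1 | Sample size calculation | Appendix 3 |
|---|---|---|---|---|
| Stenosis exactly 50% | not patent | not patent | patent | not patent |
| PSVR exactly 2.5 | not patent | not patent | patent | – |
| Angiographic restenosis only within 10 mm outside the treated segment | edges not mentioned | not patent | edges not mentioned | – |
| CT angiography only | classified | classified | no rule stated | – |

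On both cut-offs and on CT angiography, the Sample size calculation is the outlier. On the edges, Appendix 1 is the only explicit text. Only the Sample size calculation gives an order of methods, and it goes straight from invasive angiography to duplex.

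**The case against.** The strongest reply is that the intended meaning can be recovered. The Sample size calculation and Appendix 3 have the right direction, Randomization and interventions uses patent for under 50% stenosis in the run-off vessels, and planning rates of 88% to 90% cannot be rates of restenosis. Appendix 1 reads like a restenosis definition placed under the wrong label. This stands, and it limits what may be concluded.

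- A reader might infer that the trial would reward the stent with more restenosis. That requires the sponsor to code failures as successes against its own planning rates, and nothing in the article suggests this will happen.
- A reader might infer that the planned 2-point deficit vanishes. That is true only at w = 0.5, a value the article does not support.
- A reader might infer that patients imaged only by CT cannot be evaluated and would drop out. The Sample size calculation omits CT angiography; it does not exclude it. The Abstract, the follow-up instruction, Outcome measures and Appendix 1 all allow it.
- A reader might infer room to choose a definition after seeing data. The article is a condensed account, and the full protocol or analysis plan may fix the reading rules.

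The segment conflict is also softer than it looks. Outcome measures defers to the Appendix, whose target-lesion definition describes the treated segment as reaching 10 mm beyond the stent at each end. The cut-off conflicts touch only patients lying exactly on a cut-off.

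The reply does not remove the problem. The section that defers to the Appendix for detail defers to the text that is reversed throughout. The remaining differences are conflicts between stated rules, not detail left to another document.

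**Conclusion.** The point holds as an error in the stated definition of the primary end point. Outcome measures is reversed for angiography only, and Appendix 1 is reversed for both methods. The reversal is most likely a drafting error.

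The -2 to +2 point range describes literal Outcome measures scoring at the planning rates, with w unknown and equal in the two arms. It illustrates the defect and does not forecast the result. The effect of the edges, of CT angiography and of the cut-offs cannot be sized, because the article does not say how many patients they would affect. The text should be corrected before outcomes are analysed, because the noninferiority decision rests on this one definition.

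**What to change.** Use one definition in Outcome measures, the Sample size calculation and Appendices 1 and 3:

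- Patent means no occlusion and less than 50% diameter stenosis on catheter or CT angiography. If neither was done, it means PSVR below 2.5 without occlusion on duplex.
- The segment is the treated segment plus 10 mm at each end, as in Appendix 1.
- State which method prevails when a patient has more than one, including catheter against CT angiography.

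Move the present Appendix 1 wording to a definition of restenosis. Binary restenosis is a listed secondary end point and has no entry of its own in Appendix 1.

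Each element of the definition is already in the article except the full order of methods, which the sponsor has to choose. The cost is a change of wording, with no new data to collect. Recruitment was still open at publication, so the definition could be settled before outcomes were analysed.

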#### Sample size calculation

Although patency definitions varied across trials, 1-year patency rates in aortoiliac lesions were approximately 90 % on average from previous studies including CRISP-US and MELODIE [22, 23]. In the case of the SCUBA™ stent, the 9-month patency rate for the SCUBA™ stent was 99.2 % in the ACTIVE study - a prospective, multicenter, single-arm study that defines the midterm efficacy of a next-generation cobalt-chromium iliac stent for the treatment of de novo and restenotic lesions in iliac arteries [25]. However, a different definition - a ratio of <2.4 between the duplex peak systolic velocity in the treated vessel segment and the reference systolic velocity - was used, unlike the more common definition. There are limited data on the 1-year primary patency rate of the SCUBA™ stent. Based on the MELODIE trial [23], and the European multicenter iliac stent trial [26], the 1-year primary patency of the SCUBA™ stent was estimated to be 88 %, and the COMPLETE-SE™ stent was estimated to be 94.7 % in the CRISP-US trial. Therefore, the self-expandable COMPLETE-SE™ stent group will be the control group, and the balloon-expandable SCUBA™ stent group will be the experimental group.

Patency rate will be defined as absence of occlusion and absence of >50 % stenosis in the treated segment by quantitative coronary angiography (QCA) or if invasive angiography is not performed, PSVR ≤2.5 when evaluated with duplex ultrasound. On the basis of previous studies [22, 23], we hypothesize that the expected patency rate after stent deployment at 1 year would be 90 % for the self-expandable stent group, and 88 % for the balloon-expandable stent group, respectively. The predetermined noninferiority margin δ is a 10 % difference between treatment groups. There was clinical consensus that this noninferiority margin would be acceptable if safety is maintained and patients are treated more easily, regardless of stent classification. The power analysis is based on a noninferiority principle. The statistical significance level is 2.5 % at one side, the power of the test is set as 80 %, and the randomization ratio is set as 1:1. The test for proportion and the chi-square method will be used. Using standard sample size formula, it was calculated that 120 patients per group are needed for a total of 288 patients, after accounting for a 20 % dropout rate.

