There are some indirect comparative studies that compared balloon-expandable with self-expandable stents [22, 23], and one direct study that compared self-expandable with balloon-expandable stents in a human ex vivo [24]. The outcome of two different self-expanding stents (nitinol versus stainless steel) for the treatment of iliac artery lesions was indirectly compared in a multicenter prospective randomized trial. In the CRISP-US trial [22], the 9-month composite end-point rate was equivalent for the SMART stent versus the Wallstent (6.9 vs. 5.9 %), with low rates of restenosis (3.5 vs. 2.7 %), death (2.0 vs. 0.0 %), and revascularization (2.0 vs. 4.0 %) in both groups. Primary patency at 12 months was 94.7 and 91.1 % with the SMART stent and Wallstent, respectively. The MELODIE study demonstrated that The Express LD balloon-expandable stents were indirectly similar to the Palmatz balloon- expandable stent for primary patency (92.1 % at 6 months and 87.8 % at 2 years) [23]. Grenacher et al. reported that self-expanding stents presented considerably lower radial expansion force and lower degree of precision than balloon-expandable stents in a human cadaver bifurcation model [24]. However, there is no randomized comparative study that compares primary patency rates of the two different types of stent (self-expandable versus balloon-expandable) in patients with iliac artery disease.

Therefore, in this study, we will compare primary patency rates of self-expandable stents and balloon-expandable stents in real-world clinical practice. In addition, we would like to ascertain whether there are differences in safety, including the incidence of geographic miss rate and stent fracture rate, between both stent groups in steno-occlusive lesions, especially for aortoiliac bifurcation lesions.

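### The sample-size section gives two unreconciled planning rates for control-arm patency, 94.7 % and 90 %, and sizes the trial on the one more favourable to noninferiority

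*Protocol article*

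**What the plan says.** The sample-size section of the Protocol article contains two pairs of 1-year rates.

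- **First pair.** "the 1-year primary patency of the SCUBA™ stent was estimated to be 88 %, and the COMPLETE-SE™ stent was estimated to be 94.7" %. The 88 % is attributed to MELODIE [23] and a European multicentre iliac stent trial [26], and the 94.7 % to CRISP-US. From this pair the text concludes that COMPLETE-SE is the control and SCUBA the experimental arm.
- **Second pair.** One paragraph later, citing [22, 23], the plan puts its assumption as follows: "the expected patency rate after stent deployment at 1 year would be 90 % for the self-expandable stent group, and 88 % for the balloon-expandable stent group". The calculation uses this pair, with a 10-point margin, one-sided 2.5 % and 80 % power, and arrives at 120 per group.

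The only stated support for 90 % is the section's opening remark that 1-year patency averaged about that level in earlier studies whose definitions of patency varied.

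The Background shows where the figures come from. For CRISP-US: "Primary patency at 12 months was 94.7 and 91.1 % with the SMART stent and Wallstent, respectively". For MELODIE: "for primary patency (92.1 % at 6 months and 87.8 % at 2 years".

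**The concern.** The same quantity, COMPLETE-SE patency at 1 year, has two values in one section, and each carries a design decision: 94.7 % fixes the roles of the arms, and 90 % fixes the sample size. The experimental arm's 88 % is carried over unchanged, while the control arm's rate drops by 4.7 points without comment.

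In a noninferiority trial with the experimental rate fixed, lowering the control rate is not conservative. It shrinks the expected deficit and so leaves more of the margin free. If the first pair is nearer the truth, the trial would probably miss noninferiority even with both stents performing as that paragraph estimates. A reader who trusts the printed 80 % could then take the miss as evidence against the SCUBA stent.

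**Working it through.** **Inputs.** Control rate pC: 94.7 % or 90 % (sample-size section). Experimental rate pT: 88 % (both paragraphs). Margin 10 points, one-sided 2.5 %, power 80 %, 1:1 allocation (same section). Success means that the lower 95 % confidence limit for the difference lies above −10 points (Statistical analysis).

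**Formulas (normal approximation, unpooled variance).**

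- V = pC(1 − pC) + pT(1 − pT)
- n per group = (1.96 + 0.8416)² × V / (0.10 − (pC − pT))²
- power = Φ[(0.10 − (pC − pT)) / √(V/n) − 1.96]

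**Step 1: the plan's own figure.** At 90/88, V = 0.0900 + 0.1056 = 0.1956 and the free margin is 0.08. Then n = 7.849 × 0.1956 / 0.0064 = 240 per group, not the stated 120. The printed total of 288 equals 240 × 1.2, which suggests that a per-group number was read as a total. That is a separate error. It is kept apart below by showing power at both 120 and 240.

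**Step 2: the first pair.** At 94.7/88, V = 0.0502 + 0.1056 = 0.1558 and the free margin is 0.10 − 0.067 = 0.033. The variance is smaller than at 90/88, but the loss of free margin from 8 to 3.3 points dominates.

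- n = 120: standard error √(0.1558/120) = 0.0360; 0.033/0.0360 = 0.92; Φ(0.92 − 1.96) = 0.148
- n = 240: standard error 0.0255; 0.033/0.0255 = 1.295; Φ(1.295 − 1.96) = 0.253
- n for 80 %: 7.849 × 0.1558 / 0.033² = about 1,123 evaluable per group

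Put another way, the lower limit centred on the expected difference is −6.7 − 1.96 × 3.60 = −13.8 points at 120 and −6.7 − 1.96 × 2.55 = −11.7 points at 240. Both are already beyond the margin.

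**Step 3: side by side** (exact binomial enumeration of the confidence-interval rule in brackets).

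| Control/SCUBA | 120 per group | 240 per group |
|---|---|---|
| 90/88 | 51 % (52 %) | 80 % (80 %) |
| 94.7/88 | 15 % (18 %) | 25 % (27 %) |
| 91.1/88 | 42 % | 70 % |

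The last row uses the Wallstent figure from the Background, which the plan never adopts for COMPLETE-SE. At 144 per group (288 with no dropout), power is 58 % for 90/88 and 17 % for 94.7/88.

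**Step 4: dependence on the 88 %.** That figure is called a 1-year rate. From its two named sources the document shows only MELODIE's 92.1 % at 6 months and 87.8 % at 2 years; nothing from [26] is shown. Assuming linear decline between the MELODIE points, the 12-month rate would be 92.1 − (6/18) × 4.3 = 90.7 %. Against a 94.7 % control:

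| SCUBA rate | 120 per group | 240 per group |
|---|---|---|
| 88 % | 15 % | 25 % |
| 90.7 % (interpolated, assumption) | 43 % | 71 % |
| 92.1 % (6-month figure, sensitivity only) | 64 % | 90 % |

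With 94.7 % in both arms, power at 120 would be about 93 %.

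**The case against.** The plan has a fair defence on several counts.

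- **90 % is the formal planning assumption and has a stated basis.** The 94.7 % belongs to the SMART stent, not to COMPLETE-SE. Pulling one arm's favourable result from another device towards an average of earlier studies can be defended. This stands. The defect is that the section gives no such reasoning, and that the average comes from studies of both stent types while both self-expanding figures in the Background exceed 90 %.
- **80 % is claimed only under 90/88.** A reader might infer that the plan promises 80 % power at 94.7/88 and that the promise is false. The text makes no such claim.
- **The low power needs SCUBA at 88 %.** This stands too. The 88 % is itself borrowed from other stents' trials. The plan's only figure for the SCUBA stent, 99.2 % at 9 months, was noted as resting on a different patency definition. But 88 % is the value the plan uses in both paragraphs, so it is the right one for comparing the two pairs.
- **Setting 15 % against 80 % mixes two errors.** Correct. At 120 per group, power is already only 51 % under 90/88. The change attributable to this point is 51 % to 15 %, or 80 % to 25 % at 240.

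**Conclusion.** The contradiction is real. One section holds two values for control-arm patency, uses one to assign the arms and the other to size the trial, and does not connect them. At a fixed 88 % for SCUBA, the choice of 90 % over 94.7 % is worth about 36 percentage points of power at 120 per group (51 % to 15 %) and 55 at 240 (80 % to 25 %). Correcting the per-group number therefore does not settle this point.

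These sizes rest on the normal approximation, which exact enumeration supports to within about 3 points, and on 88 % for SCUBA. They do not show that 94.7/88 is the true state of affairs or that 90 % is wrong: neither 94.7 % nor 88 % comes from the stent it is assigned to, and other plausible SCUBA rates give much higher power. What the document supports is that the stated power depends on an unexplained change to one of its own estimates, in the direction that favours noninferiority.

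**What to change.** In the sample-size section:

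1. State one pair of 1-year rates as the planning assumption and justify it. If 90 % is kept for the control, say why it departs from the 94.7 % estimate, and note that 94.7 % was observed with another stent.
2. Give the basis for 88 % as a 12-month figure, including what source [26] contributes, since the MELODIE figures shown are for 6 months and 2 years.
3. Restate the power for that pair at the planned evaluable number per group, after the separate per-group error has been corrected.
4. Report power at 94.7/88 as a labelled sensitivity. A row for 91.1/88 may be added if it is marked as a literature figure and not as the plan's estimate.
5. State that under 94.7/88 a failure to show noninferiority is likely and would not by itself establish inferiority.

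The cost is a few sentences, a short table and a less favourable stated power. This point requires no change to enrolment or conduct. The article describes the trial as still recruiting, so the text can be settled before results are interpreted.

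### The sample size of 120 per group is half the 240 that the plan's own inputs require; at 90% versus 88% patency it gives about 51% power, not 80%

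*Protocol article*

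**What the plan says.** All the relevant statements are in the Sample size calculation section of the protocol article, apart from the decision rule and two related details.

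- **Design:** "The power analysis is based on a noninferiority principle", and "the self-expandable COMPLETE-SE™ stent group will be the control group, and the balloon-expandable SCUBA™ stent group will be the experimental group".
- **Assumed 12-month patency:** "would be 90 % for the self-expandable stent group" and "88 % for the balloon-expandable stent group", so a true deficit of 2 points for SCUBA.
- **Margin, error rates, allocation:** a 10-point margin, one-sided 2.5% significance and 1:1 allocation; "the power of the test is set as 80"%.
- **Result:** "it was calculated that 120 patients per group are needed", with a total of 288 after a 20% allowance for dropout.
- **A different control rate:** one paragraph before the 90% assumption, "the COMPLETE-SE™ stent was estimated to be 94.7"%, set beside 88% for SCUBA.

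The Statistical analysis section gives the matching decision rule: SCUBA is noninferior if the lower 95% confidence limit for the difference in patency lies above -10 points. It also drops patients with missing primary data and requires the intention-to-treat and per-protocol analyses to agree. The abstract gives an enrolment of 280, not 288.

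**The concern.** A sample size should follow from the inputs printed beside it, and this one does not. The gap is a factor of two.

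With 120 per group, the 95% confidence interval for the difference reaches about 7.9 points either side of the estimate. Noninferiority then needs an observed difference better than about -2.1 points, while the plan assumes a true difference of -2 points. Under its own hypothesis, the primary test is close to a coin toss.

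The harm comes at interpretation. If the lower limit falls below -10 points, readers will take it as the verdict of an 80%-power trial and count it against the balloon-expandable stent. In fact, that result would occur about half the time even if the stents performed exactly as assumed, so it would say little about whether the margin is exceeded.

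**Working it through.** **Inputs** (Sample size calculation section): control patency 0.90; experimental patency 0.88; margin 0.10; one-sided alpha 0.025 (z = 1.960); power 0.80 (z = 0.842); 1:1 allocation. The one-sided alpha matches the 95% confidence-interval rule in the Statistical analysis section.

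**Step 1. The plan's total.** 120 × 2 = 240, and 240 × 1.2 = 288. The stated total follows from 120 per group, so 120 is not a misprint within that chain.

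**Step 2. The per-group number.**

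n = (z for alpha + z for power)² × [pC(1 - pC) + pT(1 - pT)] / [margin - (pC - pT)]²

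- (1.960 + 0.842)² = 7.849, using unrounded z values
- variance sum: 0.90 × 0.10 + 0.88 × 0.12 = 0.0900 + 0.1056 = 0.1956
- distance to the margin: 0.10 - 0.02 = 0.08, squared 0.0064
- n = 7.849 × 0.1956 / 0.0064 = 239.9, so **240 evaluable per group**

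**Step 3. Other formulas, same inputs.**

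| Formula | Per group |
|---|---|
| Unpooled variance | 240 |
| Pooled variance | 241 |
| Farrington-Manning | 255 |
| Continuity-corrected | 265 |

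**Step 4. Can 120 be reached at all?** Only by departing from the stated inputs or formula.

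- Averaging the two variances instead of summing them gives 119.9.
- One-sided 5% with the 2-point difference ignored gives 121 to 122. One-sided 5% with the difference kept gives 189.
- Rates of 94.7% and 88% with their difference ignored give 123.

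Reading a per-group 240 as the total would also give 120 per group and fit 288. Which of these happened, if any, cannot be known from the article.

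**Step 5. Power at 120 per group.** SE = √(0.1956/120) = 0.0404. Then 0.08/0.0404 = 1.98, and 1.98 - 1.96 = 0.02, giving power of 50.9%. Exact binomial enumeration of the Wald confidence-interval rule gives 52.0%; Farrington-Manning gives 47.6%. The interval half-width is 1.96 × 0.0404 = 0.079.

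**Step 6. Power at 90% versus 88% for other numbers of evaluable patients** (normal approximation).

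| Scenario | Evaluable per group | Power |
|---|---|---|
| 280 enrolled, 20% lost | 112 | 48% |
| 288 enrolled, 20% lost | 115 | 49% |
| As stated | 120 | 51% |
| 288 enrolled, none lost | 144 | 58% |
| Required number | 240 | 80% |

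**Step 7. Other true rates.**

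- Both 90%: n = 7.849 × 0.18/0.01 = 141.3, so 142 per group. Power at 120 is 73%.
- 94.7% versus 88%: variance sum 0.947 × 0.053 + 0.88 × 0.12 = 0.1558; distance to the margin 0.10 - 0.067 = 0.033. n = 7.849 × 0.1558/0.033² = 1,123 per group. Power at 120 is 15% (normal) or 18% (exact).

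**The case against.** The best case against this concerns its surroundings, not the arithmetic.

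- **Power depends on the truth.** The 51% holds for 120 evaluable patients per group and true rates of exactly 90% and 88%. With equal 90% rates, power is 73% at 120 and 81% at 144 per group. With the rates reversed in SCUBA's favour, it is 84% at 120. This is right, and the 51% should always be given with its condition. But 90% and 88% are the rates on which the plan claims 80%, and even equal rates fall short at 120.
- **The 94.7% is background.** The section opens with an average of about 90% across earlier studies, and the hypothesis adopts 90% with a source. The Background section attributes 94.7% to a different self-expanding stent in CRISP-US. So 90% is the design value, and the 1,123 is not part of the arithmetic error. What remains is that the section labels 94.7% as an estimate for COMPLETE-SE, then moves to 90% without saying why, which cuts the assumed deficit from 6.7 to 2 points.
- **A failed test would still tell us something.** A confidence interval with a half-width of about 8 points does bound the difference. That is fair: such a result would be inconclusive about the margin, not empty of information.
- **A journal article is condensed.** That excuses omissions. Here the inputs and the result are both printed, and they disagree.

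**Conclusion.** The sample-size statement is wrong as written. The stated inputs require 240 evaluable patients per group, and 120 is half of that. Power under the plan's hypothesis is about 51% at 120 per group, and 48% to 58% across the range from the abstract's 280 with 20% lost to 288 with none lost. No standard formula applied to the stated inputs changes this.

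The result assumes the stated rates, margin and error level, and one primary test by the confidence-interval rule. Requiring the intention-to-treat and per-protocol analyses to agree can only lower the chance of success further. The unexplained move from 94.7% to 90% is a secondary weakness; the main error stands without it. This needs correction before results are known.

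**What to change.** Rewrite the sample-size sentence in one of two ways.

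1. **Keep the size and restate the power:** 120 evaluable per group gives about 51% power at 90% versus 88%, and 73% if both rates are 90%.
2. **Keep 80% power and restate the size:** 240 evaluable per group. Allowing for 20% dropout, that is 240/0.8 = 300 per group (600 in total), or 240 × 1.2 = 288 per group (576 in total) by the plan's own inflation.

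In either case:

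- Use one control rate, explain why it is preferred to 94.7%, and show power under both.
- Reconcile the enrolment total, which is 280 in the abstract and 288 in the sample-size section.
- State in advance how a lower limit below -10 points will be reported: noninferiority not shown, and inconclusive where the interval includes zero. An interval wholly below zero would show lower patency with SCUBA, but would not settle whether the deficit exceeds 10 points unless it also lay wholly below -10.

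The first option costs only wording and a less favourable power figure. It makes the report honest but does not strengthen the trial. The second restores the power and doubles the number of patients.
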